### Informed consent

Informed consent will be obtained from all participants before participation, in accordance with The Code of Ethics of the World Medical Association (Declaration of Helsinki) (1964). The Bioethics Committee operating within the University of Bologna raised no concern about the study (n. 0022813 dated 2024.01.06).

### Materials

**
*Instruments*
**

Individuals who agree to participate will be assessed online through a link to the questionnaires (via Psytoolkit and Qualtrics platform). The first evaluation will be carried out using an ad-hoc form to collect sociodemographic data and the following psychometric tests. 

*Santa Barbara Sense of Direction Scale* (SBSOD): The SBSOD assesses a participant’s self-reported sense of direction. The scale consists of 15 orientation-related statements (e.g. ‘I am very good at giving directions’) that participants rate on a seven-point Likert scale ranging from Strongly Agree (1) to Strongly Disagree (7). The SBSOD significantly correlates with measures of large-scale spatial skills in numerous experiments (
Hegarty *et al*., 2002;
Ventura *et al*., 2013).

*Backward Corsi Task*: The Backward Corsi Task (
Isaacs & Vargha-Khadem, 1989;
Kessels *et al*., 2008) is a cognitive tool designed to evaluate visuospatial working memory and attention by requiring participants to replicate sequences of block taps in reverse order.

The spatial performance of each participant will be measured using the following tasks.

*Spatial Configuration Task* (SCT): The Spatial Configuration Task is a quick and reliable measure of one's ability to generate and use a mental representation of the spatial configuration of different objects in a 2D virtual environment. (
Burles *et al*., 2017)

*The Rey Auditory Verbal Learning Test* (RAVLT) The Rey Auditory Verbal Learning Test (RAVLT) is a widely used neuropsychological assessment that measures verbal memory and learning. In this test, participants are presented with a list of 15 words, which they must recall across multiple trials. After a delay, they are asked to recall the list again and later recognize the words from a larger list of distractor words. The test assesses various memory functions, including immediate recall, learning ability, delayed recall, and recognition memory, helping evaluate cognitive functions related to verbal learning and memory (
Peaker & Stewart, 1989).

At the end of VSCT the SSQ will be administered to assess the feasibility of the task. The SSQ is a tool used to assess the severity and types of discomfort or sickness symptoms that individuals experience when exposed to virtual environments, simulators, or similar immersive technologies. It consists of a self-report questionnaire where individuals rate the severity of various symptoms on a 4-point scale (0 = None, 1 = Slight, 2 = Moderate, 3 = Severe) (
Kennedy *et al*., 1993).

### 
*Virtual Spatial Configuration Task* VSCT

Hardware: The task is displayed via an HTC Vive Pro Eye (display resolution of 1440 × 1600 pixels per eye and 90 Hz refresh rate) head-mounted dis-play (HMD). The HMD is equipped with an eye tracking system running at 120 Hz sampling rate and reported to achieve a spatial accuracy of 0.5° - 1.1° (
HTC Corporation, 2021;
VIVE European Union (n.d.)). Each participant is tested using the following lab setups: two SteamVR base stations ("lighthouses"; Valve Corp., Bellevue, WA,USA) are set up in the lab room for positional tracking, the lab is equipped with a VR-capable desktop computer (AMD Ryzen 9 5900HX CPU, 3.30GHz, 32GB RAM, AMD Radeon™ RX 6600M GPU). 

Software. The experiment is implemented in Unity using the Editor Version (version 2023.11f1).

**
*Scene setup*
**

To design the virtual environment, we created an empty space and selected 5 objects (a chair, a trashcan, a washer, a lamp and a plant). We chose objects that could be easily found in the house but from different rooms; this choice was made to avoid semantic facilitation or cueing in localizing the object (e.g. The table should be near the kitchen and so on) (
Lu *et al*., 2024).

Furthermore, we opted to use familiar household objects rather than the geometrical shapes traditionally employed in the Spatial Configuration Test (SCT). This decision was motivated by the unique capabilities of virtual reality, which enable the creation of immersive, ecologically valid scenarios. By selecting objects with high familiarity and recognizability, we aimed to reduce variability in object encoding and promote more consistent performance across participants. Additionally, projecting participants into environments that mirror real-life contexts—such as recognizing and remembering the arrangement of common objects within a room—enhanced both the ecological validity of the task and participant engagement.

After objects selection, the floor and the lighting are meticulously crafted. To ensure that no spatial cues such as sun position or shadow direction are given to the participant, we placed the sun directly above the head of the participant, selected “no shadows” as the shadow type for each object, and chose a uniform smooth grey floor. The objects were placed in a circular arrangement with equidistant spacing.

We use the created scene as a template for 10 different scenes, 5 dedicated to the training phase and 5 dedicated to the testing phase. 

**
*The virtual task*
**

We selected three objects for each scene: two placed near each other and a third positioned on the opposite side, facing the pair. The participant's camera was placed in front of the two adjacent objects, such that the third object was located behind them, forming a triangular spatial configuration (
Figure 1b).

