Developing a spatial task that allows users to explore the environment by rotating in a movable chair without the need for forward or backward movement not only leverages several benefits associated with gaze-directed steering (GDS) but also simplifies interaction by eliminating the need for complex movement controls, thus making VR more accessible, especially for users with limited mobility or dexterity.

 A significant advantage expected to feature this setup is represented by the reduced motion sickness. By restricting navigation to rotational exploration should avoid the sensory mismatch that often causes discomfort and enhances situational awareness, allowing users to freely observe their surroundings without the distraction of forward or backward movement.

Moreover, the design controls the visibility of virtual objects, requiring users to piece together information gradually, a feature shared also with the SCT.

This study aims to validate the newly developed VSCT by evaluating participants' performance on the original SCT both before and after VR exposure. We will use a
**between-subjects design**, dividing participants into two groups to clarify the specific effects of spatial versus non-spatial cognitive demands. One group will perform the task in virtual reality, while the other will engage in a non-spatial auditory verbal task, adapted from
Bacon *et al.* (2008), to isolate memory processes from spatial reasoning. To this end, only the first administration of the SCT (T1) will be used for correlation analyses with the VSCT, as it provides a baseline measure of spatial performance. The second administration (T2) is included solely for exploratory purposes—to investigate whether repeated exposure might lead to performance improvements and to preliminarily explore potential training effects. These exploratory findings could inform the design of future studies specifically aimed at assessing the impact of training or interventions. Establishing the VSCT’s validity is a necessary first step before we can confidently use it in such longitudinal or interventional contexts.

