We will use a series of tests and tasks to validate the VSCT. We hypothesize a positive correlation between the VSCT and SCT, as both are designed to measure the same construct—namely, the ability to form cognitive maps. We also hypothesize a positive correlation between the VSCT and Backward Corsi, as working memory is a key component in the formation and maintenance of cognitive maps (
Epstein *et al.*, 2017). Conversely, we do not expect a significant correlation between the VSCT and RAVLT. We included the Rey Auditory Verbal Learning Test (RAVLT) in our study precisely to assess discriminant validity. The RAVLT measures verbal episodic memory, while the VSCT targets visuospatial configuration memory—two constructs that are theoretically and empirically distinct (
Suri *et al.*, 2017). By including the RAVLT and confirming that it does not significantly correlate with performance on the VSCT, we provide evidence that the VSCT is not simply capturing general memory ability, but rather a more specific visuospatial memory component. This lack of correlation supports the discriminant validity of our task, helping to confirm that it measures a construct different from that assessed by standard verbal memory tasks.

Finally, to evaluate VSCT feasibility we will use the Simulator Sickness Questionnaire (SSQ) (
Kennedy *et al*., 1993).

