*Procedure*
**

 Participants will be assigned in a pseudo-randomized single-blinded manner to one of the two groups (Auditory Verbal (AV) vs. Virtual Reality (VR)). Both groups will be asked to perform an initial assessment of their spatial abilities using the 40-item version of SCT. In the next phase, the experimental group will be made to wear the "HTC VIVE" visor that will allow them to perform the Virtual Spatial Configuration Task in VR (VR condition); the control group will be administered the auditory verbal memory task (AV condition). Both groups will be given the SCT again at the end of the task (See
Figure 2). 

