**Figure 2. f2:**
[figure not shown]
Figure depicting the timelie of the experimental procedure.

**
*VR spatial task condition*
**

 Training: The participants will be placed in our virtual environment and instructed to explore the space around them in each of the scenes. In each scene, the participant will see 3 objects at a time (two in front of him and one behind him).

Testing: After the training is completed, participants will be asked to start the testing phase. This phase will last until the task is completed, namely, when the participant accurately recalls the position of the objects after three consecutive correct trials. The objects are those learned during the training phase. The participants' accuracy and reaction time will be recorded.

**
*AV memory task condition*
**

Administration of the RAVLT will involve several steps:

The experimenter will read the first list (List A) of 15 unrelated words at a rate of about one word per second. It's crucial to present the words in the same order and with the same pronunciation for each participant. After presenting the list, the participant will be asked to repeat back as many words as they can remember, regardless of the order. After the participant recalled as many words as possible from List A, the process will be repeated for five immediate recall trials. After each trial, the number of words correctly recalled will be recorded. 

The experimenter will read a second list (List A) of 15 unrelated words (List B) to the participant and instruct them to recall as many words as possible from this list. This step is designed to interfere with the participant's ability to recall words from List A. Following the presentation of List B, the participant will be asked to recall the words from List A once again. This step assesses the individual's ability to retrieve information from memory after interference.

After a short delay in which the participant will have to do a scrambled image test (usually around 20–30 minutes), the participant will be asked to recall the words from List A once more without presenting the word list again. This step evaluates the individual's ability to retain information in memory over time.

The participant's performance will be scored based on the number of words correctly recalled or recognized during each test phase.

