One of the innovative aspects of the VSCT is its potential application for populations with impaired movement. The task is designed to allow users to explore the environment by rotating in a movable chair, eliminating the need for forward or backward movement, making it particularly suitable for individuals with limited mobility or dexterity. This design simplifies interaction, reduces the complexity of movement controls, and enhances accessibility. Additionally, by limiting navigation to rotational exploration, the task minimizes the sensory mismatch that often leads to motion sickness, thereby improving user comfort and engagement. The VSCT's design strategically controls the visibility of virtual objects, requiring users to piece together information gradually. This approach encourages cognitive engagement and problem-solving as users integrate sequential observations to gain a comprehensive understanding of the environment. Such cognitive engagement is particularly beneficial for populations with impaired movement, as it provides a means to enhance spatial orientation and navigation skills without the need for physical locomotion. For instance, stroke survivors often experience limited mobility and spatial disorientation. The VSCT’s rotation-based exploration allows them to safely practice navigating a virtual environment. By gradually revealing objects as they turn, users strengthen spatial awareness and problem-solving skills without the need for walking or complex controls.

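### A single SSQ after the VSCT, with no score before the headset, describes post-task symptoms but cannot attribute them to VR or support a claim of reduced motion sickness

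*Protocol article*

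**What the plan says.** Under Validation of a new 3D spatial task, the Introduction names the feasibility instrument: "to evaluate VSCT feasibility we will use the Simulator Sickness Questionnaire (SSQ"). No other feasibility measure is given. Materials fixes the timing: "At the end of VSCT the SSQ will be administered to assess the feasibility of the task". The same paragraph describes the SSQ as rating the severity of symptoms felt in virtual environments and similar technologies, each on a scale from 0 (none) to 3 (severe).

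Materials describes the online assessment: "The first evaluation will be carried out using an ad-hoc form to collect sociodemographic data and the following psychometric tests". The tests that follow are the SBSOD and the Backward Corsi. Procedure then has both groups complete the 40-item SCT. After that, one group puts on the headset for the VSCT and the other does the AV memory task. No SSQ appears at any of these earlier steps, and none is mentioned for the AV group.

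On motion sickness, the Introduction states: "A significant advantage expected to feature this setup is represented by the reduced motion sickness". The Discussion says of rotation-only navigation that "the task minimizes the sensory mismatch that often leads to motion sickness", and adds that comfort and engagement improve as a result.

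**The concern.** A symptom score taken once, after exposure, mixes two things: how the person felt before the headset went on and what changed while wearing it. VR participants come to the headset straight from a 40-item screen task, so some tiredness or eye strain beforehand is plausible. If post-task scores turn out raised, the study will not be able to say whether the VSCT raised them. If they turn out low, it will not be able to say that rotation-only exploration made them lower than another setup would have.

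A baseline that was not collected cannot be recovered by any later analysis. The timing therefore has to be settled before recruitment and is not something an analysis plan can repair. What is at stake is the tolerability part of the report, which the Discussion uses as one of its arguments for people with limited mobility.

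**Working it through.** The article states no SSQ figure, so there is nothing to reproduce. The check is of what the planned data can identify.

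**Inputs from the article**

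- SSQ occasions in the VR group: one, at the end of the VSCT (Materials).
- SSQ occasions before the headset: none listed (Materials, Procedure).
- SSQ occasions in the AV group: none listed. The SSQ is tied to the VSCT, which that group does not perform (Procedure).
- Item range: 0 to 3 (Materials).
- Other VR setups studied for comparison: none (Procedure).

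**Step 1. What one score contains.** For each person, write

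post = pre + change.

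Only post is observed. There is one equation and two unknowns, so change is not identified.

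**Step 2. How far change is left open.** Each item lies between 0 and 3, so 0 ≤ pre ≤ 3 and

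post − 3 ≤ change ≤ post.

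The same bounds hold for means. Take a mean post-task item rating of 1 (slight), chosen for illustration only:

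| Mean rating before the headset (assumed) | Mean change = 1 − pre |
|---|---|
| 0 | +1 |
| 1 | 0 |
| 2 | −1 |
| 3 | −2 |

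The observed value is the same in every row. The lower rows are unlikely in volunteers at a university. The first two are not, and they already differ between all of the symptoms arising during the VSCT and none of them.

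**Step 3. What the score does settle.** Because pre cannot be negative, change cannot exceed post. The post-task score is therefore a ceiling on the mean change among those assessed. A low score limits how much sickness the task can have caused in them; a raised score has no clear cause.

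**Step 4. Whether it can support the word reduced.** Reduced needs a reference: another navigation mode, another VR task or a no-VR group with the same questionnaire. None is planned. Even a paired change in the VR group would show only what changed over the session, not how it compares with an alternative.

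**Step 5. People who stop early.** The VR spatial task condition section says of the testing phase: "This phase will last until the task is completed". Completion is defined there by three consecutive correct trials. The task menu has an exit option, and Consent to participate allows withdrawal at any time. The article does not say whether a person who takes the headset off early is given the SSQ. The wording can be read either way.

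**The case against.** The protocol does not promise to estimate a VR-induced change. It uses the SSQ to assess feasibility, and the post-task symptom level is a fair feasibility description. By step 3, a low score would be reassuring without any baseline. This stands: the SSQ as planned is of use, and it would be wrong to infer that the feasibility result is uninterpretable.

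The statements about motion sickness are also mostly design rationale. The Introduction words the advantage as an expectation, the Discussion argues from mechanism, and none of the hypotheses compares sickness between setups. A reader might infer that the study sets out to test reduced sickness and fails to provide a comparator. The documents do not support that. The narrower point is that the planned SSQ data cannot later be cited as evidence for the expectation.

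A reader might also infer that the worst-affected people drop out of the score and bias it downward. That is not established. No sentence says early stoppers go without an SSQ; the end of the VSCT can be read to include an end the participant chooses. A condensed article often leaves the handling of withdrawals to the full protocol, and the Figure 2 timeline is not shown. No stopping rate is given either, and with no stoppers this bias is zero. It is an ambiguity to close by wording.

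Finally, the SSQ feeds neither the sample size nor the convergent and discriminant validity analyses. That is correct and limits the importance of the point.

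**Conclusion.** The point holds in limited form. With the SSQ given once, after the VSCT and to the VR group only, the study can report symptom levels after the task. It cannot attribute those symptoms to VR exposure, and it cannot support a statement that the setup gives reduced motion sickness.

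The size in this trial cannot be stated, because the article gives no expected SSQ level, no baseline level and no stopping rate. The only range that follows from the document is the item-scale bound: the mean change may lie anywhere from the post-task mean minus 3 up to the post-task mean itself. The conclusion assumes that the steps listed in Materials and Procedure are complete as regards the SSQ. If the full protocol already schedules one before exposure, the attribution problem largely falls away and the article needs only a sentence to say so.

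This is an inexpensive improvement worth making before data collection. It does not threaten the study's main conclusions about validity.

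**What to change.** 1. Give the SSQ immediately before the headset is put on, after the first SCT, so that any symptoms from that task count as baseline.
2. Give it again at headset removal, whatever the reason for removal. This wording replaces the end of the VSCT as the trigger and covers anyone who stops early.
3. Report the mean paired change with a 95% CI alongside the post-task level, and report the number who stop early.
4. Limit the SSQ conclusion to symptom change after the VSCT. Keep reduced motion sickness as a design expectation, not a finding, since no comparison setup is studied.

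Giving the same two SSQs to the AV group is optional. It would offer a no-VR reference for change over the session, but the restricted conclusion does not need it.

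The cost is one more short questionnaire per VR participant, a few minutes each, and small changes of wording. Sample size, group assignment and the planned correlations stay as they are.

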**Figure 1. f1:**
[figure not shown]
**a.** Main menu interface presented at the beginning of each scene, allowing participants to change scenes, return to the home screen, or exit the task.
**b.** Example view of the full environment, showing all five objects placed in a triangular configuration. This layout illustrates the type of spatial arrangement participants are required to learn.
**c.** At the start of each trial, only the two front objects are visible to the participant, who must respond to a question about the missing (third) object based on memory. A floor circle indicates the location of the hidden object.
**d.** If the participant selects the wrong answer, the environment allows them to rotate and discover the third object's location. This feedback mechanism supports gradual learning of the spatial configuration.

The location of the missing object was indicated by a circle on the floor (
Figure 1c/d), providing a visual landmark to aid participants. An interactive interface allowed participants to switch scenes by pressing "change", return to the main menu with "VSCT", and exit by pressing "exit" (
Figure 1a). Participants could explore objects around them for a maximum of 20 seconds per scene.

From the beginning of the task, participants were prompted with questions about the spatial location of objects. Each scene included a canvas displaying a question (e.g., "Which object is behind you?") with three possible choices representing the missing object. Only the two adjacent objects in front of the participant were shown (
Figure 1b). Button positions were randomized to avoid spatial response biases. Participants learned the correct answers through trial and error, gradually forming internal representations of the spatial configurations based on feedback. The task consisted of 40 such trials. For each trial, the participant’s response was recorded.

**
*Environment exploration*
**

Participants could rotate and inspect the environment by moving right or left, using the Unity Interaction Toolkit and custom scripts to interface with the HMD joysticks. Users’ movements are continuous and based on the participant's head direction to ensure ecological validity with proprioceptive feedback and reduce motion sickness.

**
*Data repository*
**

At the end of the project, the project source code will be published in a dedicated public repository on Git Hub to encourage further development and research (
https://github.com/[name]/VSCT). 

**
*Procedure*
**

 Participants will be assigned in a pseudo-randomized single-blinded manner to one of the two groups (Auditory Verbal (AV) vs. Virtual Reality (VR)). Both groups will be asked to perform an initial assessment of their spatial abilities using the 40-item version of SCT. In the next phase, the experimental group will be made to wear the "HTC VIVE" visor that will allow them to perform the Virtual Spatial Configuration Task in VR (VR condition); the control group will be administered the auditory verbal memory task (AV condition). Both groups will be given the SCT again at the end of the task (See
Figure 2). 

